## Methods

### Study design

This study is a parallel-group randomized controlled trial with a 1:1:1 randomization scheme that will be conducted in West China Hospital of Sichuan University and Chengdu Second People's Hospital from April 2023 to April 2024. In this study, the Real-time and Individualized Self-management Support (RISS) program will be developed for stroke survivors guided by resilience theory. Patients will wear smartwatches (MLY B10, Huawei wrist electrocardio-blood pressure record) that can collect real-time data such as exercise, sleep, blood pressure, heart rate, and blood oxygen to prompt self-management support for transitional stroke patients. Our hypothesis is that compared with the wristband group and control group, stroke patients who receive the RISS program will have a lower incidence of recurrence rate and an improved quality of life. This study could provide new ideas for increasing patients’ self-management ability, improving quality of life, and optimizing disease outcomes. This trial protocol uses the Standard Protocol Items: Recommendations for Interventional Trials (SPIRIT) reporting guidelines (see Additional file 2). The research method conforms to the joint standard of multiarm test reports. A summary of the study design is shown in Fig. 1. Schedule of enrollment, interventions, and assessments is shown in Fig. 2.

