### Evaluation methods

An assessor-blind method is used; that is, questionnaire collectors are research assistants who are trained in the use of measurement tools but are blinded to the grouping of study subjects. The intervention effects of the three groups of patients will be measured at baseline and 2 months, 3 months, and 6 months after discharge. The evaluation content includes questionnaire surveys and biochemical index measurements. Baseline data (during hospitalization) collection: Patients will complete the assessment at the nurses’ station. Follow-up data (after discharge from the hospital) will be collected as follows: The research assistant will visit the patient at home for data collection. Patients will complete the assessment independently, but those with reading difficulties, visual impairment, or handwriting difficulties will be instructed to complete the questionnaire as each item is read to them in neutral, noncryptic language. After the evaluation, the researchers will check whether the evaluation is complete. If there are missing items, patients will complete the items on the spot and return the evaluation for verification again. Any doubts about the content will be verified with the patient on the spot. Upon completion of data collection at each follow-up time point, each study patient will receive a gift for participating in the study. Basic demographic data will be collected at baseline, including age, sex, ethnicity, education level, marital status, job status, family status, and medical condition.1. Primary outcome (for patients)

The primary outcomes are neurological function status, self-management behavior, quality of life, biochemical indicators, recurrence rate, and unplanned readmission rate.

Neurological status

The National Institutes of Health Stroke Scale (NIHSS) is the most common stroke evaluation index in the world. It covers the anterior and posterior circulation of the brain, including consciousness, movement, sensation, speech, and visual field, with a total of 15 items. NIHSS scores range from 0 to 42, with higher scores indicating more severe neurological impairment [43]. Cai Yefeng et al. introduced the NIHSS in China to conduct a multicenter and large sample test, and the results showed that the Chinese version of the NIHSS had good reliability, validity, and sensitivity [44].

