The Modified Barthel Index (MBI) will be used to assess the patient’s ability to perform ADLs. The scale contains 10 items: eating, grooming (washing face, brushing hair, brushing teeth, shaving), bathing, dressing (unfastening buttons, zipping zippers, putting on shoes and socks), bowel and urine control, toileting, bed-chair transfer, moving on the ground, and walking up and down stairs [45]. Each item is rated on a 1–5 scale as completely dependent, needing a lot of help, needing moderate help, needing little help, and being completely independent. Normal is 100 points, with a score of 91–99 indicating mild dependence; 61–90, moderate dysfunction; 21–60, severe dysfunction; and 0–20 points, completely dependent. The Chinese version has good reliability and validity [46].

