(2) Self-management behavior: The Stroke Self-management Behavior Rating Scale (SSBR) will be used to measure the level of self-management behavior of stroke patients. The scale covers 7 dimensions: disease management, medication management, diet management, daily life management, emotional management, social function and interpersonal management, and rehabilitation exercise management, with a total of 51 items. Each item is scored from 1 to 5 points, and the total score of the scale ranges from 51 to 255. The higher the score, the better the self-management behavior of the patients. The Cronbach’s *α* coefficient is 0.847, and the construct validity is 0.761. The scale has been widely used in China and has good reliability and validity [47].(3) Quality of life: The 12-item Medical Outcomes Study Short Form Health Survey version 2.0 (SF-12 v2) developed by Boston Health Research Institute will be used to measure the quality of life of patients. It has eight dimensions: general health (GH), physical functioning (PF), role physical (RP), bodily pain (BP), vitality (VT), social functioning (SF), role emotional (RE), and mental health (MH), with a total of 12 items. The total score of the GH, PF, RP, and BP dimensions is the physical component summary (PCS). The total score of the SF, RE, MH, and VT dimensions is the mental component summary (MCS), and the standardized score of each part ranges from 0 to 100. The higher the score, the better the quality of life of the patient. The total Cronbach’s *α* coefficient of the Chinese version of the questionnaire is 0.84, and Cronbach’s *α* coefficient of each dimension is greater than 0.70 [48].(4) Recurrence rate: In China, the recurrence rates of stroke patients at 3 months, 6 months, and 1 year are 12.9%, 16.0%, and 17.7%, respectively [49]. The mortality and disability rate after the recurrence of stroke will be higher, which creates a more serious burden for patients and their families. Therefore, the recurrence rate of stroke after discharge will be used as one of the evaluation indicators in this study.(5) Biochemical indicators: Blood glucose and blood pressure are important risk factors for stroke recurrence [50, 51]. In this study, the blood glucose and blood pressure of patients will be measured by a stable glucose meter (Sinocare Anzhun) and an Omron sphygmomanometer (Sinocare BA-802).(6) Unplanned readmissions: Unplanned readmissions for stroke patients are defined as unplanned readmissions to the department of neurology of a hospital for similar conditions within 30 days or less from the date of last discharge to the date of readmission. It is calculated using the following formula [52]: unplanned readmission rate = number of unplanned readmissions/total number of discharges in the group. The Health Commission of China considers unplanned readmission of stroke patients as one of the sensitive indicators of hospital return and an important indicator to evaluate the quality of hospital care [53].

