The SPSS 22.0 statistical analysis software will be used to analyze the data, and *P* < 0.05 (two-sided test) will be considered statistically significant. Count data are described by frequency/constituent ratio, and measurement data are described by mean/standard deviation according to the results of the normality test. Pearson’s chi-square test will be used to compare the count data between groups. One-way analysis of variance will be used to compare the measurement data between the three groups, and the Bonferroni method will be used for further comparison between the two groups. Repeated measures analysis of variance will be used to compare the longitudinal changes in indicators with a normal distribution. If the covariance matrix of the observed values at each time point is symmetric or spherical (Mauchly’s test, *P* ≥ 0.05), no correction will be needed. If the covariance matrix of the observed values at each time point is *P* < 0.05 (Mauchly’s test), the Greenhouse‒Geisser correction test will be used.

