This study has some limitations. First, the study population is focused on patients with ischemic stroke, and the findings may not be generalizable to patients with hemorrhagic stroke. Second, the main purpose of this study is to improve the self-management ability of patients, that is, patients are required to have a certain degree of self-care ability, so the inclusion criteria required that the BI index be greater than 40, which may have limited the participation of some severely ill patients, and these patients also need our attention. Based on the above limitations, we will extend transition management based on wearable devices to hemorrhagic stroke and critically ill patients in future research. In addition to these limitations, the data collected by the wearable devices used in the study may be inaccurate due to the device or the improper way that patients wore the device. To mitigate these risks, research assistants will repeatedly teach patients and informal caregivers about how to wear and use the device during enrollment, emphasizing the precautions, and allowing patients to practice many times until they become proficient. The wearable device used in this project is a medical-grade smartwatch that can measure blood pressure, heart rate, electrocardiogram, sleep, blood oxygen, exercise status, and other functions. It has been registered as a class II medical device by the China Food and Drug Administration and has good stability and accuracy. At present, research on the “real-time support” care model of stroke patients’ self-management could provide new ideas for breaking through the bottleneck of stroke patients’ insufficient self-management ability. The findings of this work will (1) provide evidence-based information on innovative interventions for patients with stroke during the transition period; (2) offer real-time and precise intervention for patients through wearable technology, stepping out of the original thinking of a single intervention plan, giving patients individualized intervention models based on dynamic patient data, and providing empirical evidence for the application of wearable technology in stroke patients; and (3) stimulate patients’ positive mind set and improve their adaptability in the face of adversity based on resilience theory.

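### Six unranked primary outcomes share one 0.05 threshold with no control across them, so the protocol does not settle which outcome decides the trial

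*Protocol article*

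**What the plan says.** The Abstract and Evaluation methods give the same list: "The primary outcomes are neurological function status, self-management behavior, quality of life, biochemical indicators, recurrence rate, and unplanned readmission rate". Evaluation methods then assigns measures to each domain:

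- **Neurological status:** NIHSS, and also the Barthel index ("The Modified Barthel Index (MBI) will be used to assess the patient").
- **Self-management:** one scale ("The Stroke Self-management Behavior Rating Scale (SSBR) will be used to measure the level of self-management behavior of stroke patients").
- **Quality of life:** two SF-12 summary scores, physical and mental, with no combined score ("is the mental component summary (MCS), and the standardized score of each part ranges from 0 to 100").
- **Biochemical indicators:** glucose and blood pressure ("the blood glucose and blood pressure of patients will be measured by a stable glucose meter").
- **Recurrence:** no time point is fixed.
- **Unplanned readmission:** within 30 days of discharge.

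That makes nine named variables. Assessments are planned at 2, 3 and 6 months, and none is designated primary.

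Data management and statistical analysis sets P < 0.05 once for everything ("two-sided test) will be considered statistically significant"). It plans chi-square tests, one-way ANOVA with Bonferroni between pairs of groups, and repeated measures ANOVA for longitudinal change in normally distributed indicators.

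On purpose, the Study design hypothesis is that "stroke patients who receive the RISS program will have a lower incidence of recurrence rate and an improved quality of life". The Discussion says "the main purpose of this study is to improve the self-management ability of patients", and the Abstract also describes the aim as efficacy on self-management behavior. The Sample size section uses a generic three-group ANOVA effect and names no outcome.

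**The concern.** With several primary outcomes a trial needs one of three things: a single deciding outcome, a requirement that all succeed, or control of the error rate across the set. The protocol states none of these. The Bonferroni step deals with three arms compared in pairs. It does nothing about six domains, each tested at 0.05.

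The rest of the text does not fill the gap. The stated purpose stresses one member of the list, the hypothesis stresses two others, and the sample size is tied to none.

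What is at stake is how the result can be read. No criterion for a positive trial is fixed in advance, and the chance of at least one nominally significant primary result under no effect is several times 5%. One outcome singled out in the hypothesis, recurrence, is also one that this sample size serves poorly.

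**Working it through.** **1. The plan's own sample size.** Inputs from Sample size: three groups, eta-squared 0.06, alpha 0.05, 53 per group, raised by 15% to 61 (53 × 1.15 = 60.95).

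Method: noncentral F with f² = 0.06/0.94 and noncentrality f² × N. With 53 per group, N = 159 and power is 81.4%. The figure of 53 therefore fits beta = 0.20 (exact requirement 52). The printed beta of 0.02 would need 100 per group. That misprint is a separate matter; what counts here is that 53 per group gives about 81% power for one continuous outcome at alpha 0.05.

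**2. False-positive chance across the primary set.** For k independent tests at 0.05 the chance of at least one false positive is 1 − 0.95^k:

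- k = 6: 1 − 0.7351 = 26.5%
- k = 9: 1 − 0.6302 = 37.0%

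The outcomes are probably correlated, and the protocol gives no correlations. Simulating k three-group omnibus tests (2-df chi-square, critical value 5.99) with a common assumed correlation gives:

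| Assumed correlation | 6 outcomes | 9 variables |
|---|---|---|
| 0 | 26% | 37% |
| 0.3 | 24% | 33% |
| 0.5 | 21% | 28% |
| 0.7 | 17% | 21% |

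The lowest entry, 17%, is still more than three times the nominal 5%.

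**3. Cost of keeping all six with correction.** The strictest step of Holm (or plain Bonferroni) is 0.05/6 = 0.0083. The same noncentral F calculation, with 53 evaluable per group and eta-squared 0.06, gives 58% power per outcome. Restoring 80% would need 77 evaluable per group.

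**4. Recurrence.** Evaluation methods cites a background recurrence rate of 16.0% at 6 months. The protocol states no target effect, so a halving to 8% is taken for illustration. Exact enumeration of the Pearson chi-square test for 61 against 61 gives 27% power at 0.05 and 15% at 0.05/3 = 0.0167 (three pairwise comparisons). With 53 per arm the figures are 24% and 12%. At 61 per arm, recurrence would have to fall to about 2.4% for 80% power at 0.05.

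The 95% half-width for the risk difference at 61 per arm is 1.96 × √(0.16×0.84/61 + 0.08×0.92/61) = 11.4 percentage points. If both rates are 16% it is 13.0 points.

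**The case against.** The strongest objection is that multiplicity rules and analysis time points are often left to a statistical analysis plan, which is not shown, and that a condensed article states one general threshold without calling every primary test confirmatory. That stands in part: an analysis plan could add an adjustment. It could not remove six co-equal primary outcomes from this protocol, and adjustment alone would leave the sample size short (step 3).

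Several stronger readings are tempting but not supported:

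- **Ten variables at three visits, so 30 tests and up to 79% error.** Readmission has a 30-day window, which closes before the first follow-up visit at 2 months, so it is not measured at every visit. The planned repeated measures ANOVA can give one test across visits for normally distributed indicators. The figure also needs 30 independent tests, which repeated measurements on the same patients cannot provide.
- **At least ten variables.** The text names nine. Ten requires counting systolic and diastolic pressure separately, which is usual but not written.
- **Purpose and hypothesis contradict the primary list.** Every outcome they name is on it, and the Study design section also mentions self-management just after the hypothesis. They differ in emphasis, and word order in the hypothesis is not a ranking.
- **Any single significant result will be called success.** The protocol states no success rule. It does not prevent such a claim, but it does not announce one.

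The recurrence figures rest on a cited background rate and an assumed halving, so they are illustrative.

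**Conclusion.** The point holds in this form: the protocol fixes six unranked primary outcomes, with no primary time point or success rule, under one 0.05 threshold whose only multiplicity step is between groups. Followed as written, with one omnibus test per domain, the chance of at least one false-positive primary result is about 17–26%. With one test for each of the nine named variables it is about 21–37%. In each range the upper end assumes independence and the lower end an assumed common correlation of 0.7. Repeated measures ANOVA may reduce the number of tests over time but does not control error across outcomes.

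The emphasis on self-management in one place, and on recurrence and quality of life in another, leaves the deciding outcome open. Recurrence cannot sensibly fill that role with 61 per arm. This should be settled in the protocol before outcome data are examined.

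**What to change.** Name one primary outcome at one time point: SSBR total score at 6 months. It matches the stated purpose, falls at the end of the 6-month intervention, and is a continuous score of the kind the ANOVA sizing assumes. Other continuous scales on the list would suit that sizing equally well; the stated purpose is what favours SSBR. Power stays at about 81% with 53 evaluable per group and eta-squared 0.06, with no added patients.

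Then align the Study design hypothesis with that outcome, and move the other five domains to secondary. Report recurrence as a risk difference with a 95% confidence interval, with no efficacy claim resting on it.

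If all six domains must stay primary, name one test per domain at 6 months (readmission at 30 days) and apply Holm across the six. Restate the power as about 58% per outcome at the strictest step with 53 evaluable per group, or enlarge the trial.

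The cost is a protocol amendment and a registry update. Trial status says recruitment had not started at submission and was due to begin on 10 May 2023; if it has begun since, the change should be dated and made before outcome data are examined. The downside is that five domains become supportive, although they are still measured and reported.

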### Data management and statistical analysis

The data collector guided the patients to complete the questionnaire and collected the objective data. After patients complete the questionnaire, it will be checked on the spot. If there are any unclear or missing items, the questionnaire will be corrected with the research subject on the spot. In the data entry stage, a unique identification number will be assigned to each patient, and two research assistants will use the Epidata V.3.1 software to enter and double-check the data. Any unclear or missing information will be cross-checked with the original documents and medical records. Data entry personnel will be blinded. The data in the paper questionnaire will be entered into the computer on the same day. After the data entry is completed, the paper questionnaire will be sealed in the office data storage cabinet of West China College of Nursing, and the data will be copied to the encrypted mobile hard disk and desktop computer at the same time to prevent data loss. The coordinating center is affiliated to the West China Nursing School of Sichuan University. It consists of a department chair, two staff members, a postdoc, and four graduate students. They coordinate with hospital departments and communities to ensure patient recruitment and home-based interventions. The trial steering committee is the clinical trial review team of the Ethics Committee of West China Hospital of Sichuan University (including clinicians, nurses, and full-time scientific researchers). The first review by the review team takes place prior to patient recruitment to ensure that the methods used to recruit patients meet the statistical and feasibility requirements. After that, the review team meets every 6 months to monitor until the trial is completed. At the end of the trial, a conclusive review will be conducted. During this time, they will assess the integrity of the trial process to ensure that the parties concerned are fully fulfilling their tasks and responsibilities. The data monitoring committee is composed of 3–5 staff members of the Ethics Committee of West China Hospital of Sichuan University, who will monitor the study data every 1 year. The coordinating center, trial steering committee, and data monitoring committee are independent of the sponsor and have no conflicts of interest.

The SPSS 22.0 statistical analysis software will be used to analyze the data, and *P* < 0.05 (two-sided test) will be considered statistically significant. Count data are described by frequency/constituent ratio, and measurement data are described by mean/standard deviation according to the results of the normality test. Pearson’s chi-square test will be used to compare the count data between groups. One-way analysis of variance will be used to compare the measurement data between the three groups, and the Bonferroni method will be used for further comparison between the two groups. Repeated measures analysis of variance will be used to compare the longitudinal changes in indicators with a normal distribution. If the covariance matrix of the observed values at each time point is symmetric or spherical (Mauchly’s test, *P* ≥ 0.05), no correction will be needed. If the covariance matrix of the observed values at each time point is *P* < 0.05 (Mauchly’s test), the Greenhouse‒Geisser correction test will be used.

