### Sample size

According to Polit and Beck [42], when using ANOVA to compare the means of multiple groups, the simplest method to calculate the sample size is to estimate the ratio of the sum of squared deviations between the groups and the sum of squared deviations of the total (eta-squared, *η*2). However, when there is no experimental result of the same kind of study to base *η*2, the researcher can predict whether the study effect is large, medium, or small. According to the convention, ANOVA is used to compare the means of the smartwatch group, wristband group, and control group. The *η*2 values of large, medium, and small effects are 0.14, 0.06, and 0.01, respectively. The corresponding sample sizes of the three groups are 22, 53, and 319, and the sample size of each group is 22, 53, and 319 when *α* = 0.05 and *β* = 0.02, respectively. Because there were no suitable previous research results as the basis for calculating sample size by formula, the sample size is determined by the estimation method. Taking *α* = 0.05 and *β* = 0.02, the effect is estimated to be medium, and the number of samples in each group is 53. Considering the loss of samples and other reasons to increase the sample content by 15%, we finally included 61 cases in each group for a total of 183 subjects.

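### Recurrence, one of six primary outcomes, is compared as a crude yes/no count by chi-square, although the plan expects about as many lost patients as recurrences

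*Protocol article*

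**What the plan says.** The Study design section states the hypothesis that, compared with the wristband and control groups, "stroke patients who receive the RISS program will have a lower incidence of recurrence rate and an improved quality of life". Evaluation methods lists six primary outcomes, and recurrence is one of them: "the recurrence rate of stroke after discharge will be used as one of the evaluation indicators in this study". The same section cites background rates for China: "the recurrence rates of stroke patients at 3 months, 6 months, and 1 year are 12.9%, 16.0%, and 17.7%, respectively".

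Data management and statistical analysis gives one between-group rule for outcomes of this kind: Pearson's "chi-square test will be used to compare the count data between groups". It names no time-to-event method.

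Three other places bear on whether every patient will have a six-month status:

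- Sample size allows for loss ("Considering the loss of samples and other reasons to increase the sample content by 15" percent) and arrives at 61 per group.
- Recruitment says that for drop-outs the basic information and the reason for leaving are recorded.
- Ethics and dissemination says the study leader will end a patient's participation when the patient becomes sicker.

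The abstract states that the analysis is by intention to treat. For unplanned readmission the article gives a formula with a denominator; for recurrence it gives none.

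**The concern.** Recurrence builds up over six months, but the chi-square test needs a yes or no for each patient. Someone last seen free of recurrence at month 4 has passed most of the risk but not all of it: by the cited rates, 12.9 of the 16.0 points (81%) fall in the first three months. The test cannot use those four months as they stand. The patient must be called recurrence-free, called a recurrence, or left out. Someone who dies without a documented recurrence poses the same problem.

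The choice matters because the unknowns are about as numerous as the events. It could matter more if loss differs between arms, which is plausible: the smartwatch arm has about 10 intervention contacts in eight weeks, and the other two arms have two routine telephone calls. Ending participation when a patient worsens adds a route by which loss can be tied to the outcome itself. What is at stake is a primary result that could shift with a coding choice made after the data are in.

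**Working it through.** **Inputs from the protocol.** 61 per group; 15% allowance for loss; recurrence 12.9% at 3 months and 16.0% at 6 months.

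**Assumptions.** The 16.0% applies to every arm (no true effect). The hazard is constant within months 0–3 and within months 3–6. Where arms differ, loss is 5% in the smartwatch arm and 25% in control. The protocol gives no split by arm.

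**1. The plan's own figure.** 53 × 1.15 = 60.95, so 61 per group and 3 × 61 = 183. This reproduces.

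**2. Events against unknowns.** Expected recurrences per arm: 61 × 0.160 = 9.8. Expected losses per arm: 61 × 0.15 = 9.2.

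**3. Risk already passed by a lost patient.** Hazards: −ln(1 − 0.129)/3 = 0.0460 per month, then −ln(0.840/0.871)/3 = 0.0121 per month. Averaged over a loss time uniform on 0–6 months, the cumulative risk is 10.5%.

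**4. Observed six-month rate when the true rate is 16.0%.** L is the proportion lost.

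- A: lost patients counted as recurrence-free, events before loss known, uniform loss time: (1 − L) × 16.0 + L × 10.5.
- B: lost patients counted as recurrence-free and none of their events captured: (1 − L) × 16.0.
- C: patients lost without an event dropped, events before loss kept: [(1 − L) × 0.160 + L × 0.105] / [1 − L × (1 − 0.105)].
- D: all lost patients excluded, loss unrelated to risk.

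| Coding | L = 5% | L = 15% | L = 25% |
|---|---|---|---|
| A | 15.7% | 15.2% | 14.6% |
| B | 15.2% | 13.6% | 12.0% |
| C | 16.5% | 17.5% | 18.8% |
| D | 16.0% | 16.0% | 16.0% |

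At an equal 15% loss the rate therefore runs from 13.6% (B) to 17.5% (C).

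**5. False difference between arms, 5% v 25% loss.** Under A the smartwatch arm looks 15.7 − 14.6 = 1.1 points worse; under B, 15.2 − 12.0 = 3.2 points worse; under C, 18.8 − 16.5 ≈ 2.4 points better (from unrounded values); under D there is no difference.

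**6. Scale.** The standard error of a difference between two arms is √(2 × 0.16 × 0.84 / 61) = 0.066, or 6.6 points. With losses of 5%, 15% and 25% in the three arms and coding B, the three-group chi-square rejects 7.1% of the time instead of 5%.

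**7. A true effect.** If the true rates were 8% v 16% and 3 v 15 of 61 patients were lost, coding B gives 0.08 × 58/61 = 7.6% v 0.16 × 46/61 = 12.1%, so 8.0 points shrink to 4.5. Power for 8% v 16% at 61 per arm is only about 27% before any loss.

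**The case against.** The strongest reply is that this is a missing rule and not an error. The article has one generic sentence on count data, the full protocol is not shown, and coding of loss and death may sit in an analysis plan. That is fair as far as it goes: the absence of a coding rule is not the point here. What remains is the stated test, which cannot use partial follow-up whatever rule is added.

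It can also be said that a chi-square on a fixed six-month proportion is sound if status is known for nearly everyone. That is true, but the plan itself budgets for 15% loss.

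Several features favour equal and complete follow-up: all arms have the same home assessments at 2, 3 and 6 months with a gift at each, all patients live in Chengdu, and unclear or missing data are checked against medical records. This weakens the case for a 5% v 25% split, which is only an illustration.

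A reader might infer more than the documents support:

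- That every way of coding lost patients is wrong. Excluding all of them is unbiased if loss is unrelated to risk, though it discards observed follow-up and sits badly with intention to treat.
- That unequal loss alone could create or hide a treatment difference. The computed false differences are well inside one standard error, and with power near 27% for a halving of recurrence, sampling noise dominates.
- That deaths will be scored as good outcomes. No section says so.
- That recurrence is the leading outcome. It shares the hypothesis with quality of life and is one of six primary outcomes.
- That a time-to-event analysis cures the problem alone. Censoring at last contact does not remove bias when patients leave because they are getting worse.

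**Conclusion.** The point holds in moderate form. For a primary outcome that accrues over time, the protocol prescribes a crude yes/no test while expecting about 9 unknowns per arm against about 10 events. The resulting rate depends on coding: 13.6% to 17.5% for a true 16.0% at an equal 15% loss. Under the assumed 5% v 25% loss the spurious difference is about 1 to 3 points in either direction, against a standard error of about 6.6 points, and it is zero if all lost patients are excluded and loss is unrelated to risk. These figures rest on the cited recurrence rates, piecewise constant hazards and an assumed loss split. They do not cover withdrawal linked to worsening, which the Ethics section makes possible and whose size cannot be derived from the document. The change is worth making because it is better and cheap; the trial is not invalid without it.

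**What to change.** In Data management and statistical analysis, take recurrence out of the chi-square rule and state the following:

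- The outcome is time from randomisation to first recurrence, censored at last contact.
- Report 3- and 6-month rates per arm by Kaplan-Meier, with log-rank or Cox comparisons of the smartwatch programme with control and with wristband.
- Treat death without recurrence as a competing event, using cumulative incidence for the rates where such deaths occur. Recurrence or death combined can serve as a sensitivity analysis.
- Record the dates of recurrence, death and last contact at each visit.
- For consenting patients whose participation is ended because they became sicker, keep collecting recurrence and vital status, for example from medical records. This concerns data collection only, not when participation should end.

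The cost is a few sentences of analysis text and three date fields. The visits at 2, 3 and 6 months already exist. The small downside is that event dates must be obtained at those visits or from records.
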